### Participant timeline {13}

See the participant timeline in Table 3.

**Table 3 Tab3:** During the study, laboratory tests and other complementary tests will be performed according to the clinical criteria of the physician in charge. (1) According to medical criteria. (2) This visit will be conducted by phone call or face-to-face if the physician in charge deems necessary. (3) Before administering treatment. (4) Fever in hospitalized patients with SARS-CoV-2 pneumonia is usually measured on the forehead with an infrared thermometer every 6 h or on demand, if the patient’s status so requires. (5) Fever in patients hospitalized for SARS-CoV-2 pneumonia, generally, is taken on the forehead with an infrared thermometer every 6-8 hours or on demand if the patient’s status so requires. Respiratory parameters: O2 saturation and respiratory rate. (6) Includes complete cell blood count, D-dimer, sedimentation rate, AST, ALT, bilirubin, creatinine, creatinine clearance, LDH, PT, aPTT, fibrinogen, ferritin, HDL, LDL, triglycerides, troponin, creatine-kinase, PCR, complement factor C4, C1 inhibitor antigen, and C1 inhibitor functional activity

		Visit 1	Visit 2	Visit 3	Visit 4	Visit 5	Visit 6	Visit 7 ^**(2)**^
	Patient screening	Treatment start	Hospitalization			Efficacy assessment	Hospital discharge	Study end
**Days of treatment**		**Day 1**	**Day 2**	**Day 3 (last dose)**				
**Days since the beginning of treatment administration**		**Day 0**	**Day 1**	**Day 2**	**Day 3**	**Day 10 (±1)**		**Day 28 (±3) from hospital discharge**
**Obtaining informed consent**	✔							
**Eligibility criteria assessment**	✔							
**Demographic data**	✔							
**Acute illness information (SARS-CoV-2 pneumonia):**	✔					✔		
**▫ New-onset radiological infiltrates** ^**(4)**^								
**▫ RT-PCR or antigen testing: positive**								
**General examination [respiratory parameters, fever]** ^**(5)**^	✔	✔	✔	✔	✔	✔	✔	
**General laboratory tests** ^**(6)**^	✔	✔	✔	✔	✔^(1)^	✔	✔^(1)^	✔^(1)^
**12-lead EKG**	✔	✔	✔	✔	✔	✔	✔	✔
**▫ Patient Clinical Status Scale**	✔	✔	✔	✔	✔	✔	✔	✔
**▫ Clinical Severity Assessment Scale**								
**Treatment administration**		✔	✔	✔				
**Biomarker samples**		✔^(3)^	✔	✔		✔	✔	✔
**AE, SAE and SUSAR notification**	✔	✔	✔	✔	✔	✔	✔	✔
**Concomitant treatment recording**	✔	✔	✔	✔	✔	✔	✔	

### Study procedure

Patients will be screened at the emergency department of each hospital or on the hospitalization ward on day 1 of admission. Patients enrolled on the study will be followed up until 28 days (1 month) from hospital discharge.

At the *baseline visit* (day 0, patient screening), a complete evaluation to confirm that the patient meets all the inclusion criteria and none of the exclusion criteria will be carried out. Every patient will be informed about the study and will be given the information sheet and informed consent to sign prior to enrollment in the clinical trial. Demographic parameters, medical history, information on concomitant medication, and the presence of adverse events will be recorded.

At *visit 1* (treatment start visit), a new clinical assessment will be performed. Patients will be re-evaluated to confirm (double-check) that they meet all the inclusion criteria and none of the exclusion criteria. Patients will be randomized and assigned to one of the treatment arms. Treatment will then be started. One dose of icatibant will be given every 8 h for 3 days, for a total of 9 doses, for patients assigned to the experimental group, along with SoC.

Baseline visit and visit 1 may overlap. If this occurs, the investigator will collect all the information from both visits in the electronic case report form (e-CRF).

During hospital admission (number of days may vary by length of hospital admission), all outcomes related to the patient’s clinical status and clinical severity assessment criteria will be collected daily from the medical records. All medication received by patients, as well as fluid therapy and the presence of adverse events, will also be recorded.

The following information will be retrieved until day 4 of hospitalization: general examination, vital signs (including SpO_2_), clinical data for study outcomes and adverse events assessment, 12-lead EKG, and laboratory analysis (including renal function, hepatic enzymes, and parameters suggestive of ischemia—creatine kinase, troponin). Serious adverse events (SAEs) and all any AEs will be collected, even if they are not part of the study’s endpoints or related with the investigational drug.

*Visits 2* and *3* will correspond to safety assessment during hospital admission. Visit 2 and visit 3 will take place, respectively, on day 2 (24 h after treatment start, before the 4th dose of icatibant) and on day 3 (48 h after treatment start, before the 7th dose of icatibant). *Visit 4* will take place 72 h after treatment start, end of treatment’ visit (after all doses are administered). Hospital discharge may occur after completing visit 4, if the patient is clinically stable (i.e., no fever for 48 consecutive hours without antipyretic medication, PaO_2_/FiO_2_ > 380 or O_2_ saturation > 94%, respiratory rate ≤ 24 bpm, absence of decompensation of any comorbidity).

*Visit 5* [10 (± 1) days after treatment start] will be an efficacy assessment visit. A clinical assessment will be performed and the patient’s clinical status and clinical stability criteria^#^, as well as the medication used and the presence of adverse events, will be reevaluated. If hospital discharge visit overlaps with the day 10 visit, the investigator will only complete the day 10 visit in the e-CRF, clarifying that it is also the hospital discharge visit. The patient will be sent home and will be informed of the confinement regimen measures to be followed at home (or similar, e.g., medicalized hotel), if necessary.

A patient classified as a treatment failure (i.e., non-responder—any patients who do not meet the criteria to be considered a responder) will have their participation in this study terminated. Afterwards, their condition will be treated at the discretion of the physician in charge of their particular case.

^#^Clinical stability (defined as (1) body temperature ≤ 37.5 °C for 48 h without any antipyretic medication, (2) PO_2_/FiO_2_ > 380 or oxygen saturation > 94%, (3) respiratory rate ≤ 24 rpm, and (4) the absence of any kind of comorbidity decompensation) will also be assessed and the time to achieve it will be calculated starting from the time of the baseline visit.

If the patient is discharged before the 10th day since treatment start, the investigator must complete the day 10 visit in the e-CRF for the efficacy assessment on the same day as hospital discharge.

If the patient is discharged after the 10th day since treatment start, the date of hospital discharge will be recorded (*visit 6*). The following data will also be collected at the time of hospital discharge: the patient’s clinical status and clinical stability, the number of days on invasive mechanical ventilation (if required), the number of days on antiviral treatment (if administered), AEs, and SAEs.

The end of the study visit will be performed 28 days after hospital discharge. The patient will be informed that they will be called by phone on the 28th day after hospital discharge (*visit 7*) to assess the course of the disease. Patients will also be informed that they might be requested to report for a face-to-face appointment at the hospital, if considered necessary by the physician performing the phone interview. The aim of this visit is to collate potential relapses, readmissions, or new visits to the emergency room; information on complications related to COVID-19; number of deaths from any cause and cause of death (from hospital admission and up to 28 days after hospital discharge); and presence of AEs will also be collected.

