#### Secondary outcomes

Clinical secondary outcomes are as follows: (1) “long-term efficacy”: number (percentage) of patients who reached a sustained 48-h grade 2, grade 1, or grade 0 classification on the WHO 8-point ordinal scale for clinical status assessment 10 days after starting treatment and within 28 days after hospital discharge; (2) time to achieve a clinical response: time (days) between visit 1 (treatment start visit) and the day of recording sustained 48-h grade 2, grade 1, or grade 0 classification on the WHO 8-point ordinal scale for clinical status assessment; (3) time to achieve an afebrile state: time (days) to reach a 48-h sustained afebrile state (i.e., body temperature ≤ 37.5 °C) without antipyretic medication; (4) time from symptom onset: time (days) between the first COVID-19-related symptom and visit 1 (treatment start visit); (5) number (percentage) of patients considered as responders based on National Early Warning Score 2 (NEWS 2)*. Responder is defined as a patient who reaches at least a sustained 24-h score ≤ 2; and (6) COVID-19-related relapse: number (and percentage) of patients discharged who presents a COVID-19-related relapse or comorbidity.

*Clinical severity assessment will be carried out using the NEWS 2: https://www.mdcalc.com/national-early-warning-score-news-2 [16]. This score, accessed by electronic devices, has demonstrated the ability to determine the degree of illness of a patient and prompts critical care intervention. The score is based on 7 clinical parameters (respiratory rate, oxygen saturation, any supplemental oxygen requirement, temperature, systolic blood pressure, heart rate, level of consciousness [Alert, Responsive to voice, Responsive to pain, Unresponsive]).

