## Data collection and management

### Plans for assessment and collection of outcomes {18a}

Data of interest (see primary and secondary outcomes) will be collected by the study participants’ physicians, who are familiar with this protocol. It will be collected from the anamnesis and from physical examination, which will be recorded in the patients’ digital clinical history, as well as the complementary test information. In both groups, patients will be monitored daily during the first 4 days of hospitalization and the patient’s clinical status and clinical response to treatment will be assessed.

The sponsor will oversee the maintenance of quality control systems while this study is being conducted, using standard operating procedures to do so. Data entry personnel will be given access to the participants’ digital clinical history, so that they can complete the e-CRF.

All trial-related parties accept direct access to the data source, and to the documents and reports related to the study, to be monitored and audited by the sponsor, and for inspection by the regulatory authorities. Source documents of the study must be traceable.

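### The protocol gives outcome data two end dates, hospital day 4 and discharge; if a site follows the shorter one, later recoveries may be dated late or missed in secondary outcomes

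*Protocol article*

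**What the plan says.** The collection rules stand in three places in the Protocol article.

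- **Study procedure, paragraph on the hospital admission.** For an admission of whatever length, outcomes on clinical status and "clinical severity assessment criteria will be collected daily from the medical records". The Secondary outcomes section says what severity means: "Clinical severity assessment will be carried out using the NEWS 2".
- **Study procedure, next paragraph.** "The following information will be retrieved until day 4 of hospitalization: general examination, vital signs". The same list goes on to "clinical data for study outcomes and adverse events assessment, 12-lead EKG, and laboratory analysis", so it is not confined to safety tests.
- **Section {18a}.** In both groups "patients will be monitored daily during the first 4 days of hospitalization", and the sentence goes on to the assessment of clinical status and response.

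Table 3 schedules the general examination and the clinical status scale at visits 1 to 4 (days 0 to 3 since treatment start), at visit 5 (day 10 ± 1) and at visit 6 (discharge). If discharge comes before day 10, the day-10 form is completed on the day of discharge.

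Three measures need serial readings:

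- the afebrile outcome: "time (days) to reach a 48-h sustained afebrile state", off antipyretics;
- the NEWS 2 outcome: "Responder is defined as a patient who reaches at least a sustained 24-h score ≤ 2";
- clinical stability, defined in Study procedure by 48 h without fever together with oxygenation, respiratory rate and absence of decompensation: "the time to achieve it will be calculated starting from the time of the baseline visit".

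**The concern.** The same readings have two end dates. NEWS 2 is built largely from vital signs: temperature, respiratory rate, oxygen saturation, blood pressure and heart rate. One sentence collects NEWS 2 daily until discharge. The next paragraph stops the retrieval of vital signs, and of data for the study outcomes, at hospital day 4. A site could follow either.

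The choice matters because recovery is expected late. The Concomitant treatment section expects about 90% of these patients to have a self-limited course over 7–10 days and then to be discharged. If post-day-4 readings do not reach the e-CRF, the two time measures move towards the date of discharge or day 10. Length of stay is already a separate secondary objective, so these measures would add less than intended. The trial is also open-label, with outcome data collected by the participants' own physicians at two sites, so the span of collection should not be left to local interpretation.

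**Working it through.** The plan gives no figure to reproduce here. The check sets the passages side by side and works out the gap between visits.

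**1. Does each rule cover the data each measure needs?**

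| Measure | Data needed | Daily sentence | Day-4 sentence |
|---|---|---|---|
| NEWS 2 ≤ 2 for 24 h | NEWS 2 items over 24 h | Covered by name, to discharge | Vital signs and outcome data, to day 4 |
| 48-h afebrile state | Temperature over 48 h, antipyretic use | Temperature covered only as a NEWS 2 item; medication recorded separately | Vital signs to day 4 |
| Clinical stability | Temperature, oxygenation, respiratory rate, decompensation | Saturation and respiratory rate covered only as NEWS 2 items | Examination and vital signs to day 4 |

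The two rules overlap on the vital signs and differ on when they end.

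**2. How long is the gap if only the day-4 sentence and the scheduled visits apply?**

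Inputs: visit 4 is 72 h after treatment start, which is day 3 in Table 3; visit 5 is on day 10 ± 1.

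- Nominal: 10 − 3 = 7 days.
- Earliest visit 5: 9 − 3 = 6 days.
- Latest visit 5: 11 − 3 = 8 days.
- With earlier discharge the gap ends at discharge. For example, discharge on day 7 since treatment start gives 7 − 3 = 4 days.

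The onset of an afebrile state or of stability within that interval would be known only to lie within it. Under the daily sentence the resolution is 1 day.

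**3. Is a date needed for each measure?** The two time measures need one. The NEWS 2 outcome is a count of responders, so the risk there is that a response is not captured, not that it is misdated.

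**4. From when does day 4 count?** The wording counts from hospitalization, while visit 4 counts from treatment start. If treatment starts on hospital day 1, 72 h later is hospital day 4. If it starts on hospital day 2, visit 4 falls on hospital day 5, outside the stated span. Screening takes place on day 1 of admission and may overlap with visit 1, so the two clocks will often nearly coincide, but the text does not equate them.

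**5. Do the source readings exist?** Probably. A note to Table 3 says that inpatient temperature is generally taken every 6–8 h, and the daily sentence draws on the medical records. The open question is whether the readings after day 4 must be extracted to the e-CRF.

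**The case against.** The strongest reply is that the daily sentence already covers what is said to be at risk. It names clinical severity, NEWS 2 includes temperature, respiratory rate and oxygen saturation, and medication is recorded with days of administration. The day-4 sentence also cannot be a strict cut-off, because Table 3 repeats the examination, EKG and status scale at visits 5 and 6. It fits better as the intensive safety period: the list includes EKG, troponin and creatine kinase, and the Discussion stresses monitoring during dosing and the following 24 h. Discharge after visit 4 depends on 48 h without fever, which already requires looking back through the chart. Finally, this is a condensed article, and the e-CRF field list is not shown.

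Most of this stands. A reader might infer that the outcomes cannot be dated after day 4. The documents do not support that, because it follows only if the day-4 sentence overrides the daily one. A reader might also infer a measurable loss of power or a diluted hazard ratio. That would need a recovery-time distribution and a lag from recovery to discharge, neither of which is given. The trial has no formal sample size, and the 7–10 day figure describes disease course and discharge, not time to an afebrile state.

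What the reply does not remove is the conflict itself. The shorter list names data for the study outcomes, section {18a} ties the four-day window to the assessment of response, and nothing in the text says that the window is additional to daily extraction. This is a contradiction between stated rules, not detail left to another document.

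**Conclusion.** The concern holds in a conditional form. The Study procedure section gives overlapping data two spans, and section {18a} and the visit schedule lean towards the shorter one.

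- **If the daily sentence governs,** there is no gap.
- **If a site follows the day-4 wording,** time to a 48-h afebrile state and time to clinical stability may be unresolved over up to 6 to 8 days, less with earlier discharge, for patients who recover after day 4. A 24-h NEWS 2 response in that period may not be captured.

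Only secondary outcomes are exposed. The primary outcome rests on WHO clinical status, which the daily sentence names and which is also assessed at visit 5 and at discharge. The effect on any treatment comparison cannot be derived from the document. The point should be corrected because the ambiguity falls where recovery is expected and the correction is cheap. It does not threaten the primary analysis.

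**What to change.** Reconcile Study procedure, section {18a} and Table 3 to the daily rule that is already stated:

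- State that WHO grade, temperature, antipyretic use, respiratory rate, oxygenation and all NEWS 2 items are extracted from the clinical record for each day from visit 1 to discharge, and add a note to Table 3 to the same effect.
- Describe the four-day window as the period of additional safety monitoring (EKG and laboratory tests), and take data for the study outcomes off that list.
- Say whether day 4 counts from admission or from treatment start.

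The cost is extra data entry for the later hospital days, from readings generally taken in routine care, with no new procedures. The Trial status section reports 77 patients enrolled and recruitment continuing. Because the source is the chart, the same extraction can be completed for patients already enrolled, as far as the readings were recorded.

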**Methods:**

ICAT-COVID is a multicenter, randomized, open-label, proof-of-concept phase II clinical trial assessing the clinical efficacy and safety of adding icatibant to the standard of care in patients hospitalized with COVID-19 without invasive mechanical ventilation. Patients hospitalized with a confirmed COVID-19 pneumonia diagnosis (RT-PCR or antigen test ≤ 10 days prior to randomization, and radiographic evidence of pulmonary infiltrates), rated “4” or “5” on the WHO’s clinical status scale, are eligible. Patients will be randomized on a 1:1 ratio to either standard of care-plus-icatibant (experimental group) or to standard of care alone (control group). The experimental group will receive 30 mg of icatibant subcutaneously 3 times a day for 3 days (for a total of 9 doses). The expected sample size is 120 patients (60 per group) from 2 sites in Spain. Primary outcomes are the efficacy and safety of Icatibant. The main efficacy outcome is the number of patients reaching grades “2” or “1” on the WHO scale within 10 days of starting treatment. Secondary outcomes include “long-term efficacy”: number of patients discharged who do not present COVID-19-related relapse or comorbidity up until 28 days after discharge, and mortality.

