### Outcomes {12}

#### Primary outcomes

Primary outcomes are the efficacy and safety of icatibant: number (percentage) of patients considered as responders. Responder is defined as a patient who reaches a clinical response [sustained 48-h grade 2, grade 1, or grade 0 classification on the WHO 8-point ordinal scale for clinical status assessment (Table 1)] *and* who has not presented any severe adverse events (grades “3”, “4,” or “5” of the Common Terminology Criteria for Adverse Events -CTCAE- (Table 2)) within 10 days after starting treatment.

**Table 2 Tab2:** Common Terminology Criteria for Adverse Events (CTCAE) Version 4.0

Classification	Magnitude of the adverse event
**Grade 1**	Mild adverse event. Asymptomatic or mild clinical symptoms or just an observation; intervention not indicated.
**Grade 2**	Moderate adverse event. Minimal, local or non-invasive intervention indicated.
**Grade 3**	Serious or medically significant adverse event, but not immediately life-threatening. Hospitalization or hospitalization prolongation indicated; important limitation of self-care.
**Grade 4**	Adverse event with risk of mortality or disability.
**Grade 5**	Death associated with an adverse event.

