Safety secondary outcomes are as follows: (7) number (and percentage) of patients with any AEs; (8) number (and percentage) of AEs; (9) number (and percentage) of SAEs: according to their severity and relationship with treatment, and by determining the number of patients with a grade 3, grade 4, or grade 5 adverse event according to the CTCAE (Common Terminology Criteria for Adverse Events—see Table 2); (10) mortality for any cause: number (and percentage) of patients who died; (11) COVID-19-related mortality: number (and percentage) of patients who died due to COVID-19; (12) time until death: number of days from visit 1 until death; (13) COVID-19-related complications: number (and percentage) of patients who had any complications and number (and percentage) of complications up to 28 days after hospital discharge (visit 7); (14) number (and percentage) of patients who require intensive care; (15) number (and percentage) of patients requiring intensive care and invasive mechanical ventilation; (16) number (and percentage) of patients who require oxygen supplementation from hospital discharge up until visit 7; (17) number (and percentage) of patients diagnosed with another nosocomial infection; and (18) number (and percentage) of patients who requires hospital readmission within 28 (± 3) days from hospital discharge.

Safety assessment will be carried out from the treatment’s first dose up to 28 (±3) days after hospital discharge according to the CTCAE (all AEs, SAEs, and SUSARs will be reported in the e-CRF).

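### The rule ending participation for non-responders contradicts the planned follow-up to 28 days after discharge and, taken literally, loses their outcomes after day 10

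*Protocol article*

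**What the plan says.** The protocol article, Study procedure, deals with treatment failures within its description of visit 5, the efficacy assessment at 10 (±1) days. It states that "any patients who do not meet the criteria to be considered a responder) will have their participation in this study terminated", and continues: "Afterwards, their condition will be treated at the discretion of the physician in charge of their particular case". It names no remaining survival or safety follow-up for these patients.

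Primary outcomes sets the two conditions for being a responder. The first is efficacy: "Responder is defined as a patient who reaches a clinical response [sustained 48-h grade 2, grade 1, or grade 0 classification". The second is safety, a patient "who has not presented any severe adverse events (grades “3”, “4,” or “5” of the Common Terminology Criteria for Adverse Events", within 10 days of starting treatment. Failing either one makes a patient a non-responder.

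Other parts of the article plan data beyond day 10 without limiting them to responders:

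- Study procedure, opening paragraph: "Patients enrolled on the study will be followed up until 28 days (1 month) from hospital discharge".
- Study procedure, visit 6: "If the patient is discharged after the 10th day since treatment start, the date of hospital discharge will be recorded". Clinical status, days on invasive ventilation, AEs and SAEs are collected at the same time.
- Study procedure, visit 7: relapses, readmissions, emergency visits, complications, AEs, and deaths from admission to 28 days after discharge.
- Secondary outcomes, safety list: "mortality for any cause: number (and percentage) of patients who died", together with time until death, intensive care, invasive ventilation, complications and readmission. The safety window runs from first dose to 28 (±3) days after discharge.

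**The concern.** A site holding a non-responder at day 10 has two incompatible instructions: end participation, or continue to visits 6 and 7. If it follows the first, follow-up stops because of the patient's outcome. The patients removed are those still in hospital or with a severe event, in whom later deaths, intubations and adverse events are most likely.

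Secondary comparisons of mortality, intensive care, ventilation, complications, readmission and adverse events would then no longer compare the groups as randomised. If response differs by arm, so does the missingness. Because the trial is open-label, sites could also resolve the conflict differently by arm. Hospital stay, a secondary objective, could not be measured in those who stay longest.

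The article's preference for last observation carried forward would not help. If it were applied here, a patient alive at day 10 would be carried forward as alive. No later analysis plan can recover data that were not collected.

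**Working it through.** **Could the sentence mean only that icatibant stops?** No. Dosing lasts 3 days, the illustrative schedule under Concomitant treatment puts the last dose at 64 h, and visit 4 at 72 h follows all doses. No trial treatment is left to stop at day 10, and the wording concerns participation in the study.

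**Who is visit 6 for?** In Table 1, grade 3 or higher (short of death) means hospitalised, and grades 0–2 mean not hospitalised. A patient continuously in hospital to day 10 cannot have had 48 h at grade 2 or lower, so is a non-responder. Visit 6 covers discharge after day 10, so almost everyone it is written for would already have been removed. The rare exception is someone discharged early, well for 48 h, and then readmitted.

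**Who else is removed?** A patient who recovers and goes home but had one grade 3 event within 10 days is also a non-responder, and would lose visit 7.

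**Does another section repair this?** The section on discontinuing or modifying allocated interventions {11b} keeps patients in follow-up after early termination or a treatment stop, but its commitment on outcome data covers the primary outcome only. That outcome is already settled at day 10.

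**Number of patients affected.** Inputs: N = 120, 60 per arm (Sample size); about 90% discharged within 7–10 days (Concomitant treatment). The article gives no figure for this loss to reproduce. Patients removed = N × q, where q is the non-responder share.

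- Protocol's own figure, q at least 1 − 0.90 = 0.10: 120 × 0.10 = 12 removed, 108 left. This is a floor, because response also needs 48 h sustained and no grade 3–5 event.
- Assumed q = 0.20: 120 × 0.20 = 24 removed, 96 left.
- Assumed q = 0.30: 120 × 0.30 = 36 removed, 84 left.
- If one arm had 20% and the other 30% (assumption): 60 × 0.20 = 12 against 60 × 0.30 = 18 removed.

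**Illustration for late deaths (all rates assumed).** Let m_NR and m_R be mortality after the assessment in non-responders and responders. True late mortality = q·m_NR + (1 − q)·m_R. Share of late deaths missed = q·m_NR / [q·m_NR + (1 − q)·m_R].

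- q = 0.10, m_NR = 0.10, m_R = 0.01: 0.010 / (0.010 + 0.009) = 53% missed; true 1.9%, seen in responders 1.0%.
- q = 0.20, m_NR = 0.20, m_R = 0.01: 0.040 / (0.040 + 0.008) = 83% missed; true 4.8%, seen in responders 1.0%.
- Any q with m_R = 0: 100% missed.

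Over q = 10–40%, m_NR = 10–30% and m_R = 0–1%, true late mortality is 1.0–12.6%, a responders-only count shows 0–1%, and 53–100% of late deaths are missed.

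**The case against.** The strongest reply is that this is one stray sentence. Most of the article plans full follow-up, and visit 6 makes little sense otherwise. The trial is a proof of concept with no superiority hypothesis, and its primary outcome is settled by day 10. All of that stands. It makes this an unresolved contradiction and limits the harm to secondary and safety data after day 10. It does not tell a site which instruction to follow.

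Four stronger readings are tempting, and the documents do not support them:

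- *Mortality, intensive care, ventilation and adverse events are collected only in responders.* Up to the day-10 assessment they are collected in everyone: clinical status daily during admission, and adverse events at every visit in Table 3. Only later events are at risk.
- *The trial has chosen responders-only follow-up.* The general follow-up statement, the safety window and visits 6 and 7 say otherwise.
- *Long-term efficacy cannot be computed in non-responders.* As defined under Secondary outcomes, it requires sustained grade 2 or lower at day 10, so a patient who has not reached that can be scored as a failure without later data. The main gap is in patients who reached clinical response but had a grade 3–5 event. The abstract describes the outcome differently ("number of patients discharged who do not present COVID-19-related relapse or comorbidity up until 28 days after discharge"); that discrepancy is a separate matter and adds no weight here.
- *Nearly all late deaths and intensive care stays would be lost.* The documents give no late event rates. The 53–100% range for deaths rests on assumed rates, and nothing was calculated for intensive care.

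The sentence also states no day. Day 10 is inferred from its place in the visit 5 text.

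**Conclusion.** The contradiction is real and should be corrected. Ending participation for every non-responder cannot be reconciled with follow-up of all enrolled patients to 28 days after discharge, with a safety window open to all patients, or with visits 6 and 7. Applied literally, it would remove at least about 12 of 120 patients from follow-up after day 10. That floor rests on the protocol's expectation of about 90% discharged by days 7–10. The figure of 24–36 rests on an assumed non-responder share of 20–30%. The loss would depend on outcome and possibly on arm, so the later mortality and safety comparisons would be open to bias. Nothing in the article shows that any patient has actually been terminated.

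**What to change.** Delete the termination of participation and reconcile the sections. State that:

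- every randomised patient, responder or not, is followed through visit 6 (if applicable) and visit 7 or death, unless consent is withdrawn;
- classification as a non-responder closes the efficacy assessment but not study follow-up;
- all randomised patients are the denominator for mortality and the other secondary and safety outcomes after day 10.

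The cost is a protocol amendment with IRB approval or notification, and some additional visit 7 calls. Visits 6 and 7 already exist, so no new visits are needed. Trial status reports recruitment ongoing with 77 enrolled, so a prompt change protects the patients still to come. If anyone has already been terminated, later data could be sought only as far as consent allows.
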